## Methods

### The Vincular Project aim and study design overview

Considering that the intervention proposal addressed aspects of both the body and mind, in addition to the constructs of the Self-Determination Theory, the project was named “Vincular” (the Portuguese word for “to link” or “to connect”), in the sense of intertwining, connecting, and incorporating all these elements. Additionally, the word ends in “lar” (which, when translated into English, means “home”), precisely representing the intended creation of a welcoming, safe, receptive environment free from judgment. The main objective was to promote different dynamics based on the Self-Determination Theory, with a focus on 24-h movement behaviors, especially physical activity, to reduce depression symptoms in adults from Florianópolis, a city located in the southern region of Brazil. Furthermore, as secondary objectives, the study aimed to investigate the effects of the program on indicators of 24-h movement behaviors (physical activity, sedentary behavior, and sleep) and on basic psychological needs (autonomy, competence, and relatedness), as well as verifying its role mediator in achieving primary results.

The recommendations of the SPIRIT (Standard Protocol Items: Recommendations for Interventional Trials) were followed to guide the construction of the present study [38]. The Vincular Project is a parallel-group, randomized controlled clinical trial with blinding of the primary, secondary outcomes, and other variables, following the design outlined by Hulley et al. [39]. It consists of two arms (a control group and an intervention group) and is conducted at a single center. This study was registered in the Brazilian Registry of Clinical Trials (ReBEC) under the identification code RBR-7466htj, and submitted to the Research Ethics Committee involving Human Subjects at the Federal University of Santa Catarina (CEPSH-UFSC), obtaining a favorable opinion (Opinion Number 5.622.082; CAAE 60378122.1.0000.0121). The informed consent form was made available online, accessible for download, and participants indicated their agreement or disagreement to participate in the research.

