To investigate the mediating role of basic psychological needs, structural equation modeling procedures will be adopted, using linear regression models, through the lavaan package in the RStudio software (version 2021.09.0). Diagrams will be created using the “Miro” website (https://miro.com). For the structural equation model, the “SEM” command will be utilized with the MLM estimator: maximum likelihood estimation. In this context, the mediating variable corresponds to an intervening factor essential for completing the causal relationship between an independent variable and a target behavior [129]. In intervention studies, a variable is considered a mediator when it alters the positive relationship between the treatment and the investigative variable (exemplified, in the present study, by the CG and IG and by depressive symptoms, respectively). Different analyses can be employed to identify mediating variables, based on statistical procedures that test the hypothesis that an independent variable (treatment) influences a certain outcome (investigative variable) through one or more mediators [130]. For this type of analysis to occur, a causal chain with at least three variables (independent, mediating, and dependent) is necessary, as illustrated in Fig. 3. In this model, the independent variable (treatment) is represented by “X,” while the mediating variable is “M,” and the dependent/investigative variable, “Y.” Thus, the model assumes a system with different possibilities: (a) the treatment impacting the investigative variable, referred to as the total effect (represented by coefficient “c”); (b) the treatment impacting the mediating variable (coefficient “a”); (c) the mediating variable impacting the dependent/investigative variable, with adjustment for the treatment variable (coefficient “b”); and (d) the treatment impacting the investigative variable, adjusting for the mediating variable, known as direct effect (coefficient “c”). The indirect effect of the treatment on the investigative variable through the mediating variable is calculated as the product of coefficients “a” and “b.” The total effect is calculated by summing the direct and indirect effects (c = c’ + ab) [130].

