**Fig. 4 Fig4:**
[figure not shown]
Description of the model of possible mediating variables of the Vincular Project. Source: own authorship (2023). Notes: total effect of the treatment on the investigative variable (coefficient “f”); mediated direct effect of the treatment on the investigative variable (coefficient “f’”); effect of treatment on basic psychological needs (“a” coefficients); effect of the treatment on the investigative variable, including the basic psychological needs variables (coefficients “a” and “b”)

The variables used in the models will take into account the difference between post-intervention and baseline values. The effect of the intervention on depressive symptoms will be observed directly, obtaining the total direct effect of the intervention. Subsequently, all paths for potential mediating variables will be included to determine the indirect effects of treatment on depressive symptoms. Two models will be tested: the first with the observed variables, represented by the overall PHQ-9 score and the individual autonomy, competence, and relatedness scores; and the second model, considering latent variables, corresponding to each PHQ-9 question and the basic psychological needs instrument. For statistical modeling, the “backward” selection strategy will be adopted, with a critical level of *p* ≤ 0.20 for variables to remain in the model. The following adjustment indices and cutoff points will be utilized: (a) degrees of freedom (df) ≥ 1; (b) chi-square *p*-value (X2) > 0.05; (c) ratio X2 per df < 3; (d) comparative fit index (CFI) and Tucker–Lewis index (TLI) > 0.90; (e) root mean square error of approximation (RMSEA) < 0.08; (f) RMSEA *p*-value < 0.05; and (g) standardized root mean square residual (SRMR) < 0.08 [132].

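### The protocol's only statement of when a need counts as a mediator is met by every sample, and the nearby p ≤ 0.20 retention rule does not test the indirect effect either

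*Protocol article*

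**What the plan says.** Mediation is a secondary objective. The aim section of the protocol article lists effects on the basic psychological needs, "as well as verifying its role mediator in achieving primary results".

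The mediation text under Data treatment and statistical analyses then states:

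- **Criterion:** "a variable is considered a mediator when it alters the positive relationship between the treatment and the investigative variable". The same sentence names the control and intervention groups and depressive symptoms as this study's example.
- **Indirect effect:** "The indirect effect of the treatment on the investigative variable through the mediating variable is calculated as the product of coefficients" a and b.
- **Decomposition:** "The total effect is calculated by summing the direct and indirect effects", that is, c = c' + ab.
- **Testing, in general terms:** mediation methods are described as procedures that "test the hypothesis that an independent variable (treatment) influences a certain outcome (investigative variable) through one or more mediators". No particular test is chosen.
- **Software and estimator:** "structural equation modeling procedures will be adopted, using linear regression models, through the lavaan package", and "the “SEM” command will be utilized with the MLM estimator: maximum likelihood estimation".
- **Variables:** the observed-variable model uses change from baseline to post-intervention in "the overall PHQ-9 score and the individual autonomy, competence, and relatedness scores". All three needs enter as mediators together.
- **Selection:** backward, with variables kept at p ≤ 0.20, followed by a list of model-fit cutoffs.

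Two other thresholds stand elsewhere in the section. The p ≤ 0.05 level is in the GEE paragraph, and the 95% intervals belong to the descriptive statistics. Neither is tied to a×b.

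**The concern.** A criterion for mediation has to be one that a non-mediator can fail. To alter the treatment–outcome relationship means that the coefficient of arm changes once the need is in the model, and some change always occurs. Confounding of the need with symptoms, or suppression, would produce it as well. The sign is also off. PHQ-9 runs from 0 to 27 with higher scores worse, so with the intervention arm coded above control a beneficial effect is negative.

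A reader looking for a sharper rule nearby finds only p ≤ 0.20 retention. That concerns whether a term stays in a model, not whether the intervention acts through it.

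At stake is the mediation objective. With three candidate needs, the published text gives no basis for saying which of them, if any, carried an effect.

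**Working it through.** **1. Sample sizes.** The plan states 28, doubled to 56 for 50% dropout. With f = 0.25, two groups, three time points, alpha 0.05 and an assumed within-person correlation of 0.5, λ = f²·N·m/(1−ρ) = 0.0625 × 28 × 3 / 0.5 = 10.5 on 2 and 52 df. Power is 81.2%, and 28/(1 − 0.5) = 56. Both figures reproduce, so n = 28 and n = 56 bracket the mediation analysis.

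**2. The criterion.** From c = c' + ab, c − c' = ab. This is an exact identity for least-squares fits of linear models, and a numerical check found no difference beyond rounding (below 1e-15). With continuous estimates ab is never exactly zero, so c' differs from c in every sample, including those drawn with a true indirect effect of zero. No effect size has to be assumed. With three needs in one linear model, the difference between total and direct effect is a₁b₁ + a₂b₂ + a₃b₃. A change in the arm coefficient therefore does not even say which need produced it.

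**3. The p ≤ 0.20 rule.** Suppose retention is decided on b. Assume 1:1 arms, unit residual SDs, a = 0 and b = −0.39, so true ab = 0. Given the residual sum of squares S of the need (chi-square, n − 2 df), the t statistic for b is noncentral t on n − 3 df with noncentrality −0.39√S. Maximum-likelihood standard errors divide by n, so |z| ≥ 1.282 is the same as |t| ≥ 1.282·√((n − 3)/n).

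- n = 28: cut-off 1.211, retained in 77%.
- n = 56: cut-off 1.247, retained in 94%.
- With ordinary t tests instead: 74% and 93%.

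With b = 0, a need is kept in about 20% of trials by t test. At least one of three is kept in 1 − 0.8³ = 49% if they are independent.

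**4. An interval for a×b.** This used simulated single-mediator trials with true ab = 0 (6,000 per scenario; a from 0 to 0.8, b of 0 or −0.5). A 95% Monte Carlo interval excluded zero in 0.2% to 3.6% of trials at n = 28 and 0.1% to 4.8% at n = 56. With b = 0 and a very large a (1.5 to 2 SD), the rate at n = 28 rose to about 6 to 8%, of which roughly half lay in the direction of lower PHQ-9.

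Power with true mediation (1,500 trials per scenario; path values assumed):

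| n | a | b | Normal-theory z | Monte Carlo interval | Gain (points) |
|---|---|---|---|---|---|
| 28 | 0.5 | −0.39 | 5.2% | 13.1% | 7.9 |
| 28 | 0.8 | −0.39 | 13.9% | 28.3% | 14.4 |
| 28 | 0.8 | −0.59 | 31.4% | 47.6% | 16.2 |
| 28 | 1.0 | −0.50 | 36.5% | 54.4% | 17.9 |
| 56 | 0.5 | −0.39 | 20.2% | 36.5% | 16.3 |
| 56 | 0.8 | −0.39 | 50.8% | 68.8% | 18.0 |

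A repeat of the first row with small-sample standard errors gave about 4% against 11%, a gain of 7 points.

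**The case against.** The strongest reply is that the sentence is textbook prose and not a decision rule. It opens with intervention studies in general and sits among cited definitions. The text around it calls a mediator a link in a causal chain, refers to hypothesis tests and defines a×b correctly. This stands in part. The sentence is not clearly operative, but it is the only one saying when a variable counts as a mediator, and it is mapped to this trial.

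Other parts of the reply also stand:

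- A reader might infer that mediation would be declared by chance in 100% of trials. The documents do not support that. The 100% describes the wording, and nowhere does the article say a claim follows whenever c' differs from c.
- A reader might take 'alters' to mean a percentage change in c. No such cut-off is stated, so no error rate can be attached to one.
- A missing interval for a×b is by itself no finding, since an analysis plan not shown may name one.
- False claims from 'alters' and lost power from the default z rest on different readings and cannot both be charged to the plan. The article does not say that a z test decides.
- The article does not state that p ≤ 0.20 applies to the mediator paths, so step 3 is conditional.
- 'Positive' may be a translation of 'beneficial'. No calculation uses it.

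**Conclusion.** The point holds as a fault in a published definition, whatever a separate analysis plan may add. The stated criterion cannot discriminate, by the article's own algebra and without any assumption. The one coefficient-level threshold in the mediation text does not repair it. If applied to the mediator paths, it keeps a need with no indirect effect in about 77% (n = 28) to 94% (n = 56) of trials at the assumed a = 0 and b = −0.39.

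An interval for a×b keeps false claims at or below about 5% in most null scenarios. At the assumed paths it gains roughly 7 to 18 points of power over the normal-theory z for a×b. These rates come from single-mediator models with normal errors, whereas the plan has three mediators at once and a latent-variable model, so they are indicative. It would go too far to conclude that the plan will produce chance mediators or that MLM is the wrong estimator. The weight is moderate: a secondary objective is affected and the primary GEE analysis is not.

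**What to change.** Replace the criterion with: *A need is called a mediator only if the 95% Monte Carlo (or percentile bootstrap) confidence interval of its specific indirect effect a×b excludes zero, in the direction of lower PHQ-9.* Add that retention at p ≤ 0.20 is not evidence of mediation, and correct 'positive'.

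The Monte Carlo interval needs only the estimates of a and b and their covariance matrix, which MLM supplies, so the estimator can stay.

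The cost is wording and a few lines of R. Fewer variables will be called mediators, and at n = 28 the interval's error rate can slightly exceed 5% when a is large.

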**Fig. 3 Fig3:**
[figure not shown]
Paths of the mediation model. Source: adapted from Hayes [130]

Considering that behavior change interventions aimed at reducing depressive symptoms can involve complex and multidimensional processes, it is unlikely for this outcome to be solely explained by a single mediator. In this context, multiple mediation models will be explored, which simultaneously considering basic psychological needs as potential mediators in the relationship between treatment and depressive symptoms [130, 131], as illustrated in Fig. 4. In this model, the following paths are observed: (a) the total effect of the treatment on the investigative variable (coefficient “f”); (b) the direct effect of the treatment on the investigative variable, with adjustment for the mediating variable (coefficient “f’”); (c) the effect of treatment on basic psychological needs (“a” coefficients); and (d) the effect of the treatment on the investigative variable, including the basic psychological needs variables, which assume the role of mediators (coefficients “a” and “b”).

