Another assumption of Self-Determination Theory is that the level and quality of motivation experienced by individuals during the performance of an action are determined by the perceived value of that action in satisfying three fundamental psychological needs: autonomy, competence, and relatedness [32, 34]. Autonomy refers to actions that are self-endorsed, freely chosen by the individual, leading to a sense of ownership and personal responsibility. Competence corresponds to the perception of effectiveness in interactions with the environment, of mastering and expanding your capabilities and skills, making them challenging, until personal growth is achieved. The relatedness revolves around the desire for belonging, close emotional relationships, and the need to feel accepted and respected, fostering a sense of connection and mutual concern. It is evident that these basic psychological needs are innate and intricately linked to intrinsic motivation, self-regulation, and overall well-being. They explore the processes and conditions that facilitate healthy development and effective functioning of the individual [32]. Additionally, it is highlighted that these psychological needs are interdependent, suggesting that “the satisfaction of one need supports the satisfaction of the other two needs” [34].

Whether an individual’s basic psychological needs are satisfied or frustrated depends on the extent to which the subject’s environment and relationships support or harm these needs [34, 35]. Behaviors or messages from social agents (such as health professionals, family, friends, and colleagues), who operate within an individual’s social environment, or information obtained through various channels like magazines, newspapers, or social networks, can contribute to changes in psychological needs [36]. For example, if these behaviors, messages, or content support the satisfaction of psychological needs, individuals will presumably experience their actions as autonomously motivated, enabling the engagement and/or maintenance of health behaviors [34–36].

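### The stated fit rules do not suit the full three-need observed-score mediation model: with the needs' residual covariances free it has no degrees of freedom, and with them fixed at zero global fit tests only whether the needs are uncorrelated

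*Protocol article*

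**What the plan says.** The mediation plan is in the protocol article, section Data treatment and statistical analyses, in the paragraphs around Figs. 3 and 4.

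- **Model.** The three needs enter together, "which simultaneously considering basic psychological needs as potential mediators in the relationship between treatment and depressive symptoms". The text and the Fig. 4 notes name a total effect f, a direct effect f', the a paths and the b paths: "c) the effect of treatment on basic psychological needs (“a” coefficients); and (d) the effect of the treatment on the investigative variable". No covariance among the needs is mentioned. At the start, "all paths for potential mediating variables will be included to determine the indirect effects of treatment on depressive symptoms".
- **Variables.** All are change scores, post-intervention minus baseline. There are two versions of the model: one on the observed PHQ-9 and need scores, one on latent variables built from the items.
- **Estimation.** The lavaan SEM command "will be utilized with the MLM estimator: maximum likelihood estimation".
- **Selection and fit.** Backward selection retains terms at p ≤ 0.20. One list of fit criteria covers both versions. It opens with "a) degrees of freedom (df) ≥ 1" and goes on to chi-square p > 0.05, chi-square/df < 3, CFI and TLI > 0.90, RMSEA < 0.08 and SRMR < 0.08.
- **Theory.** The section Theoretical basis of the Vincular Project says "it is highlighted that these psychological needs are interdependent" and cites the view that "the satisfaction of one need supports the satisfaction of the other two needs".

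**The concern.** In a parallel mediation model on observed scores, global fit carries information only about what the model leaves out. Here the only candidates before selection are the three residual covariances among the needs. Whether they are free or fixed decides whether the fit criteria can be applied at all, and what they test.

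At stake is the secondary objective of whether the needs mediate the effect on depressive symptoms. An acceptance rule that rejects the full three-need model for a reason unrelated to mediation would push the analysts to re-specify the model after seeing the data. If they instead kept a zero-covariance model that had failed, the b paths would carry standard errors that ignore the overlap between needs.

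**Working it through.** **Sample size used.** The article gives no figure for the mediation model. Its trial size is 28, doubled to 56 for dropout. The 28 reproduces as a within-between interaction with f = 0.25, 2 groups, 3 times, and an assumed repeated-measures correlation of 0.5 with sphericity. λ = f²·N·m/(1 − ρ) = 0.0625 × 28 × 3/0.5 = 10.5 on 2 and 52 df gives power 0.812; N = 26 gives 0.778. I use n = 28 and n = 56 as the two ends.

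**Degrees of freedom.** Five observed variables give 5 × 6/2 = 15 moments.
- Covariances at zero: 3 a paths + 3 b paths + 1 direct path + 5 variances = 12 parameters, df = 3.
- Covariances free: 12 + 3 = 15 parameters, df = 0.

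**What the 3 df test.** With the directed paths saturated, the likelihood-ratio chi-square reduces to T = −n ln|R|, where R is the residual correlation matrix of the three needs given arm. PHQ-9 does not enter it. For equal correlations ρ, |R| = (1 − ρ)²(1 + 2ρ). The 5% critical value on 3 df is 7.81.

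**Standard errors of b.** Fixing the covariances at zero removes the variance inflation from the reported error. The ratio of reported to correct standard error is 1/√VIF, with VIF = 1/(1 − 2ρ²/(1 + ρ)). At ρ = 0.5, VIF = 1.5 and the ratio is 0.82.

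The article gives no ρ, so the range is an assumption. Simulation set-up: 1:1 arms, a = 0.5, b = 0, −0.3, −0.3, normal errors.

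| ρ | −ln\|R\| | T implied by ρ, n = 28 / 56 | Fails chi-square rule, n = 28 / 56 | SE ratio for b |
|---|---|---|---|---|
| 0.2 | 0.110 | 3.1 / 6.1 | 32% / 54% | 0.97 |
| 0.3 | 0.243 | 6.8 / 13.6 | 59% / 87% | 0.93 |
| 0.5 | 0.693 | 19.4 / 38.8 | 95% / over 99% | 0.82 |

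The scaled (Satorra-Bentler) chi-square gives nearly the same failure rates: 34%/52%, 58%/86% and 94%/100%. At ρ = 0, where the zero-covariance model is true, it still fails in 10%/7%. RMSEA is 0.08 or more in 41%/29% at ρ = 0 and 71%/82% at ρ = 0.2.

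**Does MLM repair the errors?** No. At n = 56 and ρ = 0.5 the mean MLM standard error of a null b path is 0.128, against a true standard deviation of 0.176. The a paths are essentially unaffected (0.262 against 0.271).

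**Does this produce false mediators under the plan's rule?** Over all simulated trials at n = 56, a null b path is declared significant at the 5% level in 16% at ρ = 0.5, against 9.5% at ρ = 0. Among trials that pass the chi-square rule, the rate stays near its ρ = 0 level across ρ = 0 to 0.3: about 13% at n = 28 and 8 to 9% at n = 56 with robust errors. That excess over 5% is small-sample behaviour, not the omitted covariances.

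**Backward selection with free covariances.** Each path dropped adds one df. If every path survives p ≤ 0.20, df stays at 0 and the df rule fails, so the model whose paths are all retained is the one the rule turns away. If paths are dropped, the df come from paths just removed as non-significant, so the fit check is largely circular.

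**The case against.** The strongest reply is that nothing in the article fixes the covariances at zero. It names directed effects with coefficient letters; it does not list the variances either, and nobody would take those as fixed. Fig. 4, where double-headed arrows would appear, is not shown, and a condensed article may leave such syntax to the full plan or code. This stands: a reader might infer that the plan contradicts its own theory, but the text does not say so.

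The reply also notes that the fit list serves the latent model too, which has df of its own, and that a reduced observed-score model gains df. This stands as well, so the problem is confined to the full observed-score model.

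A reader might further infer that single needs will be declared mediators too often. The documents do not support that. The inflation from omitted covariances arises only if a model that fails the fit rule is kept, and the article does not plan that.

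Finally, ρ is undocumented and mediation is secondary; the primary GEE analysis is untouched. At ρ = 0.2 the standard-error bias is slight. That is correct, and it limits the size of the point. What the reply does not remove is that the fit rules are stated in full and do not suit the full observed-score model under either reading.

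**Conclusion.** The point holds in conditional form. The df counts (0 or 3) follow from the model and need no assumption about correlation. With the covariances free, the full observed-score model cannot meet df ≥ 1. With them at zero, which is inferred, global fit tests only the absence of correlation among needs that the article describes as interdependent.

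How often that rejects the model depends on an assumed residual correlation between change scores: roughly a third to a half of trials at 0.2, and nearly all at 0.5. Certain failure is not shown. Too-small standard errors concern the b paths, and through them the indirect effects, only in a zero-covariance model kept despite failing. The latent model was not computed. This is worth correcting because a stated acceptance rule can reject the full model for reasons unrelated to mediation.

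**What to change.** In the paragraphs around Fig. 4:

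1. State that the residual covariances among autonomy, competence and relatedness are freely estimated in the observed-score model, and likewise the covariances among the need factors' disturbances in the latent model.
2. Drop df ≥ 1 and the global fit indices as an acceptance gate for the observed-score model while it is saturated. Judge it on its path and indirect-effect estimates.
3. Keep the fit indices for the latent model and for any reduced model that is over-identified.

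The cost is three extra lines of lavaan syntax and a sentence or two of text. The standard errors for single needs will be wider than in a zero-covariance model, reflecting how far the data can separate the needs.
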